##### Covariables

A questionnaire created by the authors is used to gather sociodemographic (age, sex, level of education, marital and professional status, number of children, and income) and clinical data (MBS date, medical conditions, and weight). The accuracy of the self-reported clinical data will be verified at the end of the study by reviewing the participants’ medical records. Smoking status (nonsmoker, smoker, or former smoker) is self-reported, and unhealthy alcohol consumption is assessed using the Alcohol Use Disorder Identification Test-Concise [103].

Sedentary time (hours/day), light PA (min/week), and daily step count is assessed using accelerometers with the following threshold values used for analyses: sedentary time ≤100 counts/min, light-intensity PA=100-1951 min/week [83]. The Global Physical Activity Questionnaire [104] is also completed by the participants to obtain self-reported PA data because it allows for the estimation of participants’ levels of PA during previous 7 days in 3 domains (work, travel to and from places, and recreational activities), which is not possible with accelerometers [104]. Total self-reported MVPA (min/week) will be calculated by summing the MVPA scores for transportation, leisure, and work. The question— “How much time do you usually spend sitting or reclining on a typical day?”—in the Global Physical Activity Questionnaire will be used to assess self-reported sedentary time.

Pain is assessed using the *RAND*-36 Physical Pain subscale, which consists of the following two validated items: (1) How much bodily pain have you had during the past 4 weeks? (2) During the past 4 weeks, how much did pain interfere with your normal work (including both work outside the home and housework)? An average score will be computed, whereby higher levels will reflect greater pain levels.

### The TELE-BariACTIV Intervention

During phase B1, participants will receive 6 real-time, face-to-face sessions with the same PA counselor (to the extent possible) over a 6-week period before MBS. The sessions will last approximately 45 minutes and will be conducted via videoconferencing using Zoom. The TELE-BariACTIV intervention is a multicomponent intervention derived from a previous intervention by Bond et al [22,28,29], which was developed based on multiple theories, including SDT and SCT, and was revised by the current research team. The intervention targets SDT and SCT constructs, focusing specifically on (1) providing autonomy support, structure, and interpersonal involvement; (2) increasing perceptions of autonomy (ie, perceived control over one’s actions by providing a rationale, structure, and emphasizing responsibility), competence (ie, perceived mastery of tasks and skills by providing support and encouragement, information feedback, and support barrier identification), and relatedness (ie, perceived belonging and connection to others by encouraging to seek social support); (3) increasing autonomous motivation for PA (ie, acting through self-endorsement and volition because the activity holds inherent interest or personal value); and (4) fostering perceived self-efficacy to overcome PA barriers and engage in PA. Accordingly, the intervention integrates several content- and relational-based techniques hypothesized to target the theoretical constructs. The techniques are selected on the basis of the theoretical construct or constructs they are proposed to target, wherein the research team drew on published literature [105-108] to determine which techniques target specific SDT and SCT constructs to guide the selection. The MBCTs used to guide the content of the intervention sessions during phase B1 are presented in Table 2.

In addition, the PA counselor uses motivational interviewing techniques [108] (ie, empathic or reflective listening, asking open-ended questions, prompting the participant to ask questions, prompting participants to offer solutions, seeking permission to provide information and advice, shifting focus, supporting change or persistence, and showing unconditional regard) that align with SDT and SCT for the relational component of the intervention to support the delivery of the content. The goal of the intervention is to address participants’ mindset about PA, as well as their motivation to engage in PA, with the goal of supporting PA uptake and maintenance. To this end, participants are encouraged to progressively increase their daily PA to achieve the current PA guidelines of 150 minutes per week of MVPA by the end of phase B1 (before MBS) and to maintain or increase PA levels during phases B2 (after MBS) and A3 (at the 1-year follow-up). Owing to the goal of helping participants increase and maintain PA after MBS, participants are offered 3 booster sessions to discuss progress or relapses and work on PA psychosocial and cognitive processes already addressed during phase B1. These sessions are one-on-one sessions, occur at 1-month intervals, and are conducted via videoconferencing using Zoom. They last 45 minutes, though they can be shorter as the topics are not pre-established; rather, the participants are free to choose the topics according to their needs. Length and topics discussed are recorded by the PA counselor.

**Table 2 table2:** Overview of the telehealth bariatric behavior intervention^a^.

Session number and overview	Topics	Content- and relation-based techniques (motivation and behavior change techniques, and motivational interviewing techniques)
1. Welcome to the trial	Discuss importance of PA^b^ within context of bariatric surgery Identify health risks of a sedentary lifestyle and health benefits of an active lifestyle Evaluate perceived benefits and personal barriers related to PA adoption Establish baseline daily average PA minutes and steps Discuss PA target Provide PA monitoring logbook, pedometer, and instructions for recording daily bout-related walking exercise minutes and steps Provide information about the benefits and costs of action or inaction to participants	Review specific guidelines for PA participation Discuss benefits of PA and elicit participants’ reasons for increasing PA Examine cost and benefit of current PA behavior and changing behavior Acknowledge any internal conflict regarding PA adoption Offer clear rationale for PA adoption Self–re-evaluation (explore congruence between values, goals, and lifestyle) Assess motivational readiness *Shaping knowledge*: Instruction on how to perform the behavior, and how to monitor behavior and affect *Comparison of outcomes*: Credible source, pros and cons *Natural consequences*: Information about health consequences
2. Goal setting for behavior resolution	Introduce goal-setting principles, set goals targeting behaviors to increase PA Identify pleasant or unpleasant aspects of PA Differentiate extrinsic and intrinsic motives and rewards Identify ways to make PA more enjoyable	Review SMART^c^ goal approach Facilitate short- and long-term goal development Emphasize enjoyable aspects of PA *Goal setting*: Goal setting, problem solving, action planning, discrepancy between current behavior and goal, review outcome goal or goals, behavior contract, and commitment *Self-belief*: Verbal persuasion about capability, focus on past success, and self-talk *Natural consequences*: Information about health consequences, salience of consequences, monitoring of emotional consequences, and anticipated regret *Scheduled consequences*: Reward alternative behavior
3. Building a preoperative PA program	Differentiate lifestyle and structured PA Brainstorm ways to increase lifestyle PA Teach talk test to gauge PA intensity Discuss making PA a habit Record of PA behavior Record of outcomes related to PA Instruction to perform behavior Prompt practice	Review methods of self-monitoring Encourage the use of a self-monitoring technique to evaluate progress postintervention *Goal setting*: Goal setting, problem solving, action planning, discrepancy between current behavior and goal, review outcome goal or goals, behavior contract, and commitment *Feedback and monitoring*: Feedback on behavior, self-monitoring of outcome or outcomes of behavior, self-monitoring of behavior *Self-belief*: Verbal persuasion about capability, focus on past success, and self-talk *Reward and threat*: Self-reward *Associations*: Prompts or cues
4. Creating an active environment: Making physical and social cues work for you	Environmental restructuring Identify positive environmental cues to increase PA Provide information on where and when to perform PA Identify strategies to eliminate or avoid inactivity cues Plan social support or social change	Review main types of social support Encourage participants to examine social network Develop reasons and plans to include others in their lifestyle changes Have participants examine their current environment and determine methods for creating a PA-promoting environment *Goal setting*: Goal setting, problem solving, action planning, discrepancy between current behavior and goal, review outcome goal or goals, behavior contract, and commitment *Feedback and monitoring*: Feedback on behavior, self-monitoring of outcome or outcomes of behavior, and self-monitoring of behavior *Antecedents*: Restructuring the physical environment, restructuring the social environment, and body changes *Social support*: Social support (unspecified), social support (practical), and social support (emotional)
5. Resolving issues and planning	Problem-solving Action planning Barrier identification or problem solving Increasing self-efficacy	Elicit potential barriers that participants may experience Develop plans to overcome barriers *Goal setting*: Goal setting, problem solving, action planning, discrepancy between current behavior and goal, review outcome goal or goals, behavior contract, and commitment *Feedback and monitoring*: Feedback on behavior, self-monitoring of outcome outcomes of behavior, and self-monitoring of behavior *Self-belief*: Verbal persuasion about capability, focus on past success, self-talk *Repetition and substitution*: Behavior substitution
6. Putting it all together and establishing commitment or habit	Develop new contract to facilitate commitment to maintenance of PA change consisting of short-, medium-, and long-term goals Relapse prevention or coping planning	Behavior contracting or self-liberation Social support or helping relationships Self–re-evaluation Mastery experiences *Goal setting*: Goal setting, problem solving, action planning, discrepancy between current behavior and goal, review outcome goal or goals, behavior contract, and commitment *Self-belief*: Verbal persuasion about capability, focus on past success, and self-talk *Feedback and monitoring*: Feedback on behavior, self-monitoring of outcome or outcomes of behavior, and self-monitoring of behavior *Antecedents*: Restructuring the physical environment, restructuring the social environment, and body changes *Social support*: Social support (unspecified), social support (practical), and social support (emotional) *Repetition and substitution*: Habit formation *Associations*: Prompts or cues

^a^Behavior change technique groupings refer to the hierarchically clustered 93 techniques presented in the behavior change technique taxonomy (v1), are italicized, and specific techniques to be used follow the colons.

^b^PA: physical activity.

^c^SMART: specific, measurable, attainable, relevant, time-based.

In addition, participants are encouraged to use the provided PA monitor (A370 Polar watch) for the study duration to track their PA behavior (not for research data collection), as this has been shown to be an effective way to increase goal setting, self-monitoring, and overall PA adherence [109,110].

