## Methods

### Study Design and Procedures

The study uses a phased approach to behavior change intervention development supported by the Obesity Related Behavioral Intervention Trials model [31].

The study results will be reported according to the recommendations for single-case protocols in behavioral interventions [75]. Owing to the objectives of the study (feasibility, acceptability, and effect size exploration) and recommendations [31,76], this study is a multicenter study with a single-case experimental design with multiple base levels (ABAB’A). It is an open-label trial in which research staff, researchers, and participants are not blinded to the study objectives, intervention, and allocation, given the nature of the intervention and measures.

Approximately 2 weeks before the baseline assessment, the study will be explained by phone to potential participants and the selection criteria, checked. Eligible and interested participants will be sent an accelerometer and a A370 Polar (Polar Electro) watch with cables to recharge and information sheet by mail with a prepaid return envelope. Participants will be instructed to initiate the baseline assessment on the web (Limesurvey) once they receive their packages, including an informed consent form. Then, participants will be randomly allocated to a 1- or 2-week baseline A1 phase using a list of random numbers generated electronically by a person outside the project, and they will start the 5 phases of the study (A1-B1-A2-B2-A3; Figure 1). The A phases are observational phases without intervention, and the B phases are intervention phases with PA counseling delivered via Zoom technology platform. Participants had different dates of starting the study owing to the variability in their MBS dates. Phase A2 may also vary in length because the exact MBS date is usually not known when participants are to start the study.

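### The activity watch is supplied before baseline and encouraged throughout, so A1, A2 and A3 are not intervention-free as described, and A1–B1 estimates counseling added to self-monitoring

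*Protocol article*

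**What the plan says.** Four statements in the protocol article bear on the watch.

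- **Supply.** Study Design and Procedures: "Eligible and interested participants will be sent an accelerometer and a A370 Polar (Polar Electro) watch with cables to recharge". The same paragraph continues: "Participants will be instructed to initiate the baseline assessment on the web (Limesurvey) once they receive their packages". Allocation to a 1- or 2-week A1 phase follows. Participants therefore hold the watch before A1 begins.
- **Use.** The TELE-BariACTIV Intervention, after Table 2: "participants are encouraged to use the provided PA monitor (A370 Polar watch) for the study duration to track their PA behavior". The sentence adds that the watch does not serve research data collection, and gives the reason for it: "as this has been shown to be an effective way to increase goal setting, self-monitoring, and overall PA adherence".
- **Phase definition.** Study Design and Procedures: "The A phases are observational phases without intervention, and the B phases are intervention phases with PA counseling delivered via Zoom technology platform". The Abstract describes the A phases in the same way, and Principal Findings says that they do a job similar to that of an untreated control group.
- **Use of the contrast.** Under Statistical Analyses, daily MVPA in A1 and B1 is compared within each participant by a randomization test, and the individual effect sizes are pooled by meta-analysis. The pooled effect is to supply the sample size of the large-scale trial. Under Objectives, the quantity wanted is the effect of TELE-BariACTIV on presurgical MVPA.

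Table 2 lists self-monitoring of behavior among the techniques of sessions 3 to 6. Session 1 has its own monitoring item: "Provide PA monitoring logbook, pedometer, and instructions for recording daily bout-related walking exercise minutes and steps". How the pedometer relates to the watch is not stated.

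**The concern.** By the article's own account the watch has one role, to change behavior, and it is described within the intervention section. If its use is encouraged from the first day of the study to the last, part of the package is present in every A phase. The statements on supply and use cannot then stand beside a definition of those phases as having no intervention.

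What is at stake is the second objective. A1 is the reference for the effect that is to size the next trial. If A1 already contains part of the package, the comparator is misdescribed and the estimate answers a narrower question than the one set under Objectives. The ABABA comparison has the same difficulty, because A2 and A3 are also treated as intervention-free.

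**Working it through.** The article states no figure that depends on this point. The 12 participants are justified by convention for single-case designs, without an effect size, SD or power, so there is nothing to reproduce. The check has three steps.

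**1. Do the passages conflict?** The watch is in hand before A1, and the encouragement covers the whole study. Nothing says that the watch is withheld, masked or left unused in A1, and Limitations does not mention it. Taken literally, the statements on supply and use contradict "The A phases are observational phases without intervention".

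**2. What does A1–B1 estimate?** Let C be the effect of counseling on daily MVPA, and W_A1 and W_B1 the effect of the watch in each phase.

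- Contrast: B1 − A1 = C + W_B1 − W_A1.
- Target 1, the full package, is C + W_B1, so the bias is −W_A1.
- Target 2, counseling alone, is C, so the bias is W_B1 − W_A1.

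With assumed values in min/day and C = 10:

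| W_A1 | W_B1 | Contrast | Bias against package | Bias against counseling |
|---|---|---|---|---|
| 3 | 3 | 10 | −3 | 0 |
| 5 | 2 | 7 | −5 | −3 |
| 2 | 5 | 13 | −2 | +3 |
| 0 | 4 | 14 | 0 | +4 |

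Against the package, the contrast is too small whenever W_A1 is positive. Against counseling alone, the sign depends on how the watch effect changes between phases.

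**3. What could this do to the future sample size?** Suppose a share w of the package effect is already present in A1. The estimate is then (1 − w) times the package effect, and a sample size derived from it grows by 1/(1 − w)². The illustration below assumes a package effect of 0.5 SD, two parallel arms, two-sided alpha 0.05 and power 0.80. None of these values, nor w, comes from the article.

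| w | Effect seen (SD) | n per arm | 1/(1 − w)² |
|---|---|---|---|
| 0 | 0.50 | 63 | 1.00 |
| 10% | 0.45 | 78 | 1.23 |
| 20% | 0.40 | 99 | 1.56 |
| 30% | 0.35 | 129 | 2.04 |
| 50% | 0.25 | 252 | 4.00 |

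This also assumes that the pooled single-case effect carries over directly to a comparison of groups, and that future controls have no watch.

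**The case against.** The strongest reply is that early use is not proven. The article describes a single mailing. The encouragement appears only in the intervention section, and instruction in monitoring comes at B1 session 1 with the logbook and pedometer. The mailed information sheet and the counselor manual are not shown, and either might delay use of the watch. This stands as a limit on what can be claimed about actual wear. It does not remove the contradiction, because the article says when the watch is sent, how long its use is encouraged and why, and nowhere excepts A1.

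A second reply is that the B phases are defined by counseling. On that target a constant watch effect cancels, and a growing one biases the contrast upward. This is correct, and it makes the direction conditional. Objectives and the intervention section favor the full package as the target, but the condition has to be stated. Likewise, the comparator of the future trial is not given. If its controls also had a watch, A1–B1 would be the relevant contrast.

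A reader might go further and infer that watch novelty fades, so that 1- and 2-week baselines are affected unequally and a randomized comparison is disturbed. The documents do not support this. They say nothing about how a watch effect changes over time. Baseline length is randomized, but the planned test compares A1 with B1 within each participant, and no comparison of 1-week with 2-week baselines is planned.

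**Conclusion.** The contradiction holds. The watch is supplied before baseline and encouraged throughout on the ground that it works, while the A phases are presented as intervention-free and control-like. As written, A1–B1 estimates counseling added to watch self-monitoring.

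It may be tempting to conclude that the estimate is biased toward zero as a matter of fact. That needs three conditions: the watch is used in A1, it raises MVPA there, and the full package is the target. Only the third has support in the text. If all three hold, the contrast understates the package effect by an amount that the article does not allow to be computed, and a trial sized on it would be larger than needed rather than underpowered.

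Only the second objective and the wording about the A phases are affected.

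**What to change.** **For anyone not yet in A1, and for the future trial:** release or activate the watch at B1 session 1, with the logbook and pedometer, so that A1 has the accelerometer only. The cost is a second mailing or a delayed activation. Results reports all 12 participants enrolled by July 2022, so within this study the change reaches only those who have not started A1.

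**For participants already enrolled:**

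- Establish the date of first watch use, from the device record or by one question at the next contact.
- Where the watch was used in A1, report A1–B1 as counseling added to self-monitoring.
- Add a sensitivity analysis by watch use in A1 if numbers allow. If nearly all used it, few or no participants would be left without it.
- Carry the caveat into the future sample size calculation, and state there whether future controls will have a watch.
- Reconcile the two sections, and stop describing A phases with watch use as free of intervention or as equivalent to an untreated control.

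These steps cost one question per participant, a short extra analysis and changed wording.

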### Internal Validity

During the individual interviews, the participants are asked about all life events or factors that occurred during the study period (eg, divorce, injuries, illness, lockdown, and new employment) that may have impacted the study results. This strategy allows for greater certainty in confirming whether any changes observed are related to the intervention [111].

### Statistical Analyses

Descriptive statistics will be computed for baseline sociodemographic, clinical, feasibility, and acceptability data derived from the numerical responses and close-ended questions.

All statistical analyses will be carried out using R and the following packages: scan, SCRT [112], metafor, ggplot2, and tydiverse. For the primary outcomes of a future large-scale trial, a comparison of daily MVPA based on accelerometer data between phases A1 and B1 will be carried out using a randomization test for a single-case experimental design [113] for each participant. Subsequently, individual effect sizes will be aggregated in a meta-analysis to obtain a group-based effect size. This will provide the necessary information for computing the required sample size for a future large-scale trial. A sensitivity analysis will also be performed to compare A1 and B1 using a Tau-*U* test [114]. Then, a second meta-analysis will be performed using the same approach. The global effect of the intervention on daily MVPA will be tested using another set of randomization tests comparing the ABABA phases. This test makes it possible to compare 2 short time series and to provide an effect size in case of a significant difference. This analysis will be performed on an individual scale.

Generalization measures (secondary outcomes for a future large-scale trial: health-related quality of life, anxiety, and depression symptoms) will be analyzed using the Reliable Change Index or cutoff score for descriptive purposes; the differences in individual scores across phases will be compared [115].

Theoretical construct measures (secondary outcomes for a future large-scale trial: PA enjoyment, motivational regulations for PA, basic psychological needs satisfaction and frustration, self-efficacy to overcome PA barriers, and social support for exercise) and self-reported MVPA will be analyzed using visual analysis. As recommended [116], stability, mean level change, and range of data by phase will be examined.

Content analysis of participants’ responses to open-ended questions during the interviews and of the PA counselors’ notes completed after the session will be conducted to identify themes and see if or what changes to the protocol or methods or intervention are warranted [117]. This will involve five steps, which will be followed by 2 research staff members: (1) familiarize themselves with the data by reading each transcribed interview several times before coding and looking for patterns, (2) code the transcripts and compile the initial codes, (3) put together similar codes to form potential themes and subthemes, (4) review the main themes and subthemes in relation to the data, and (5) define and name themes, select illustrative quotes from the interviews and produce a report.

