**Secondary outcomes**				
	**Behavior targeted: MVPA^a^ (primary outcome for a future large-scale trial)**			
		MVPA (min/days)	Accelerometer (Actigraph)	8; during the 7 or 14 days of the phase A1, during 7 days before phase B2, mid- and after phases B1 and B2, as well as 6 and 12 months after MBS^b^ (phase A3)

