### Participants

Participants are adults residing in or around 3 cities (ie, Montreal, Quebec City, and Chicoutimi) in the province of Quebec (Canada) and receiving care at either one of 2 tertiary care centers (Institut Universitaire de Cardiologie et de Pneumologie de Québec-Université Laval and the Centre Intégré Universitaire de Soins et de Services de Santé [CIUSSS] du Nord-de-l’Île-de-Montréal) or at a regional center (CIUSSS du Saguenay–Lac-Saint-Jean). Recruited strategies include (1) placing posters in waiting rooms at the target centers and (2) asking health professionals from hospitals at each site to refer to potentially eligible patients. For the latter, health professionals will provide the research team with the name and contact information of patients who have a planned sleeve gastrectomy in >12 weeks and who have provided verbal consent to be contacted by the research team for information on the study. The target sample size will be 12 (approximately 4 per site), which is considered acceptable for a single-case experimental study with multiple base levels, as participants serve as their own control, and outcomes will be measured repeatedly across observational and interventional phases [75,77].

The inclusion criteria are (1) ≥18 years of age; (2) scheduled to undergo sleeve gastrectomy in >12 weeks in one of the 3 associated hospitals (University Institute of Cardiology and Pulmonology of Quebec, Quebec; Sacré Cœur Hospital, Montreal [CIUSSS du Nord-de-l’Île-de-Montréal]; Chicoutimi Hospital, Chicoutimi [CIUSSS Saguenay–Lac-Saint-Jean]) Qc, Canada); (3) self-report ≤150 minutes of MVPA per week; and (4) access to a computer with internet and an interface with a camera. Exclusion criteria are (1) having a contraindication to PA without medical clearance (the Get Active questionnaire from the Canadian Society for Exercise Physiology [78] is used to determine if medical clearance is needed); (2) already enrolled in a supervised exercise intervention or PA behavior change intervention; (3) inability to speak and understand French; and (4) need a wheelchair, cane, walker, or other support or supports to move.

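### With only a 1- or 2-week baseline randomised, a randomization test within one participant can give no p-value below 0.50

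*Protocol article*

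**What the plan says.** Study Design and Procedures describes one random element: "participants will be randomly allocated to a 1- or 2-week baseline A1 phase using a list of random numbers".

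The other phase lengths are not randomised. For B1, the intervention section says that "participants will receive 6 real-time, face-to-face sessions with the same PA counselor (to the extent possible) over a 6-week period before MBS". For A2, the design section says: "Phase A2 may also vary in length because the exact MBS date is usually not known when participants are to start the study".

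Under Statistical Analyses, the comparison of daily accelerometer MVPA between A1 and B1 "will be carried out using a randomization test for a single-case experimental design [113] for each participant". The individual effect sizes are then pooled by meta-analysis to size a later trial, and Tau-U with a second meta-analysis serves as sensitivity analysis. A further set of randomization tests compares the ABABA phases, again at the level of the individual. The sentence after the ABABA test says that the test makes it possible "to provide an effect size in case of a significant difference".

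Table 1 places the accelerometer windows before and around the intervention phases "during the 7 or 14 days of the phase A1, during 7 days before phase B2, mid- and after phases B1 and B2". The article states no alpha, no sidedness, no set of permitted start points and no randomization test across participants.

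**The concern.** A randomization test compares the observed statistic with the values it would have taken under the other allocations that could have been drawn. Its smallest attainable p-value is one divided by the number of equally likely allocations. With two baseline lengths per participant that number is very small, and nothing later in the sequence adds to it.

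What is at stake is how the individual results are read. Twelve non-significant tests could be taken as evidence that the intervention did nothing, when the test could not have shown anything else. In addition, if effect sizes from these tests are given only when the test is significant, none will ever be given.

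**Working it through.** The plan gives no minimum p-value or power for this test, so there is no figure of its own to reproduce.

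**Inputs from the article**
- Allocations of A1 per participant: 2 (1 or 2 weeks), from Study Design and Procedures.
- Random elements in B1 and A2: none.
- Unit of the test: one participant, for both the A1-B1 and the ABABA comparisons.
- Participants: 12 (Participants; all enrolled according to Results).

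**Assumptions:** the two lengths are equally likely, and alpha is 0.05 (not stated in the article).

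**Floor for one participant**
- Minimum p = 1 / (number of allocations) = 1/2 = 0.50.
- If the observed allocation gives the larger statistic, p = 1/2 = 0.50. Otherwise p = 2/2 = 1.00. No other value is possible.
- Check by simulation: 20,000 daily series with a level shift of 10 SD at the true start of B1 gave p = 0.50 every time.
- Allocations needed for p ≤ 0.05: 1/0.05 = 20. The design has 2.
- The ABABA test adds phases but no random element, so its floor is also 0.50.

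**Reference sets that the design did not randomise**

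With n measured days and at least 3 days in each phase (an assumption), the number of start points is n − 6 + 1.

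| Days A1 + B1 | Start points | Minimum p |
|---|---|---|
| 7 + 7 | 14 − 5 = 9 | 0.111 |
| 7 + 14 or 14 + 7 | 21 − 5 = 16 | 0.0625 |
| 14 + 14 | 28 − 5 = 23 | 0.043 |

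Only the last row falls below 0.05, and a participant with a 1-week A1 cannot be in it. Shuffling all days of a 7 + 7 series gives 1/3432 = 0.0003. In each of these sets, most of the rearrangements could not have been drawn, so the randomisation does not support the p-value.

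**Joint test over the actual allocations**
- 12 independent two-way allocations: 2^12 = 4096, so minimum p = 1/4096 = 0.00024.
- If the list was restricted, the number is smaller. With a fixed 6:6 split it would be C(12,6) = 924, so minimum p = 1/924 = 0.0011.

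**Data needed for the alternative allocation**
- A participant given 2 weeks, had they been given 1: days 8 to 14 would count as B1. They were measured as part of A1.
- A participant given 1 week, had they been given 2: days 8 to 14 would count as A1. They actually fell in the first week of B1. Table 1 lists B1 windows only in the middle of and after the phase, so this week appears to have no scheduled measurement.

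**The case against.** **The reference set is not named.** The article does not say which start points the software will permute over, and the cited method sources are not at hand. Some choices would give p below 0.05. This stands as a limit: the floor of 0.50 belongs to the test based on the allocation actually made. It does not rescue the plan, because the other choices lack support from that allocation.

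**The second objective survives.** A reader might infer that the estimate for the future trial fails. The documents do not support that. The aim is an effect estimate, and the pooled effect size can be computed with no individual p-value.

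**Selective pooling.** A reader might infer that only significant participants enter the meta-analysis and that the pooled effect is then too large. The documents do not support this either. The significance condition follows the ABABA test, while the sentence that sends A1-B1 effect sizes to the meta-analysis carries no condition. Moreover, if no test can be significant, there is no significant subset to select.

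**Tau-U.** It would be too strong to say that no planned analysis can show a significant individual effect. Tau-U is not bound by the floor.

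**The missing week.** The timing of the windows is referred to Figure 1, which is not shown, and participants are told to wear the device continuously, so unscheduled data may exist. This part is therefore probable rather than certain.

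**Conclusion.** The point holds as a mismatch between the stated test and the stated randomisation. Under the allocation described, each of the 12 A1-B1 randomization tests, and each individual ABABA test, can return only 0.50 or 1.00. None can reach a conventional significance level at any effect size. This needs no assumption about variance, autocorrelation or the size of the effect. It assumes only that the two baseline lengths are equally likely and that the reference set is the set of allocations the design could have produced.

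The consequence is limited. The individual p-values carry no inferential information, and an effect size that depended on significance would never be reported from these tests. The pooled estimate, the Tau-U analysis and the feasibility and acceptability outcomes, which are primary here, are not affected.

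**What to change.** - Drop the per-participant randomization p-values for A1-B1 and ABABA, or label them as descriptive and non-inferential.
- Report each participant's A1-to-B1 difference in min/day with an interval, whatever its size.
- State that all participants' effect sizes enter the meta-analysis.
- Remove from Statistical Analyses the condition that ties an effect size to a significant difference.
- If a randomization test is kept, run one joint test across the 12 participants over the allocations that could have been drawn (up to 4096). First confirm that accelerometer data exist for the first week of B1 in participants given a 1-week A1. Say that power may be low, because only one week of the sequence is randomised.

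The cost is analysis wording only. No new data or participants are needed. Enrolment is complete, so the number of possible allocations can no longer be increased. What is given up is a set of p-values that could not have been informative.
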